## Abstract

**Background:**

Nonspecific neck pain is a multifactorial and very common condition in adult individuals, traditional acupuncture (TA) and laser acupuncture (LA) may be treatment options for certain individuals in such a condition. However, no reports were found in the literature comparing the effectiveness of TA and LA in cases of chronic nonspecific neck pain. Therefore, the aim of the present study is to investigate the effectiveness of TA and LA therapies in individuals with chronic nonspecific neck pain, noting which one is more efficient for this condition. The result of this research will have direct implications for pain management and, consequently, may benefit individuals suffering from nonspecific chronic neck pain.

**Methods/design:**

This will be a controlled and randomized clinical trial. Eighty-four individuals will be recruited and distributed equally and randomly into 3 groups: TA (which will receive the acupuncture treatment with needles), LA (which will receive the laser acupuncture treatment), and Sham (who will receive the placebo intervention). The acupuncture points (*Tianzhu*, *Fengchi*, *Jianjing*, and *Jianzhongshu*) will be stimulated bilaterally. The primary outcome will be pain intensity, determined using the Numerical Rating Scale. The secondary outcomes will be pressure pain threshold, temporal summation of pain, conditioned pain modulation, use of analgesic medicines after treatment, and the global perceived effect scale. The assessments will be performed immediately before and after the treatment, which will be a single session, at the follow-up and 1 month after the end of the treatments; evaluation will be made of the pain intensity and the global perceived effect. Statistical analysis of the data obtained will consider a significance level of *p* < 0.05.

**Discussion:**

This study will provide evidence concerning the effects of LA treatment, in comparison with TA and sham intervention, leading to benefits for individuals suffering from chronic nonspecific neck pain.

**Trial registration:**

Brazilian Registry of Clinical Trials - ReBEC RBR-7vbw5gd. Date of registration: August 06th, 2021.

## Administrative information

*Note: The numbers in curly brackets in this protocol refer to SPIRIT checklist item numbers. The order of the items has been modified to group similar items.

## Introduction

### Background and rationale {6a}

Neck pain is a very common condition that causes considerable disability and economic losses [1, 2]. Between the years 1990 and 2017, high indices of neck pain were reported in 195 countries, so it can be considered a serious global public health problem, ranked fourth among the causes of disability, with an annual prevalence rate higher than 30% [2, 3]. It is more common in women and usually increases with age, reaching peaks in the age groups 45–49 and 50–54 years for men and women, respectively, with a decrease for older persons [2]. Several risk factors are associated with neck pain, including obesity and a sedentary lifestyle. It results in restrictions and disabilities that can have major impacts on the physical, social, and psychological well-being of the individual [2, 4, 5]. Neck pain can be classified according to its etiology. It is considered specific when there are anatomical changes resulting from dysfunctions in neck structures, such as the deterioration of nerve roots, capsule damage, nerve root compression, or fractures [3]. Nonspecific neck pain is multifactorial in nature and is not associated with a specific disease or anatomical modification [6, 7]. Neck pain is classified according to the duration of symptoms, being acute (up to 1 month), subacute (1 to 3 months), and chronic (at least 3 months) [8–10]. Chronic neck pain is defined as any continuous pain in the cervical spine region between the base of the head and the upper shoulder, lasting at least 12 weeks and usually accompanied by reduced cervical movement [11].

Various strategies can be used for the treatment of neck pain, including acupuncture, which originated over 3000 years ago and constitutes part of traditional Chinese medicine [12–15]. The technique, performed with needles, produces good results and is effective in reducing pain and disability [16–23]. It has been shown to provide clinical benefits in individuals with neck pain, so it is a viable option for use by health services [24]. It is considered a safe treatment, with serious side effects being rare, compared to conventional techniques used for the treatment of pain [25, 26].

There are now alternative acupuncture techniques available that do not use needles, such as laser acupuncture (LA), which combines the use of the traditional Chinese acupuncture points with stimulation by laser light energy [15, 27, 28]. The lasers most indicated for LA are red or infrared, due to their deeper penetration into human tissue, with powers in the range from 5 to 500 mW (Low-Level Laser Therapy (LLLT)) [28–30]. Laser acupuncture acts to enhance enzymatic defense systems, increasing plasma levels of superoxide dismutase (SOD), glutathione reductase (GRd), reduced glutathione (GSH), and catalase. It assists in maintaining the integrity of the redox cycle and can promote reductions of malondialdehyde (MDA, a plasma marker of oxidative stress), the inflammation markers C-reactive protein (CRP) and interleukin-6 (IL-6), and glutathione peroxidase (GPx). It can reduce oxidative stress damage, inflammation, joint edema, and pain in patients with rheumatoid arthritis [31].

An obvious difference between acupuncture using needles and LA is that the laser enables the stimulation of acupuncture points without damaging the skin tissue [30]. The laser induces a photochemical reaction in the cells, in a process known as photobiomodulation, at acupuncture points selected using the same rules as traditional Chinese acupuncture [32, 33]. Using an optical power of around 40 mW, the effect of LA is similar to that obtained with metal needles [28], so it can be an attractive option for the treatment of chronic pain [34].

Acupuncture using needles is a widely accepted technique that provides good results and can be effective in reducing chronic neck pain [16, 17, 19, 20, 35–44].

Meanwhile, the clinical use of LA is increasing, since it offers the advantages of being totally painless, non-invasive, and safe [30, 33, 43], and it can be used with people who have a phobia of needles. There are few studies in the literature using LA for cervical and pain conditions, such as chronic cervical syndrome, myofascial pain syndrome, spondylosis, temporomandibular disorders, and musculoskeletal pain, with positive results, strengthening the use of laser acupuncture [39, 45–48].

However, more studies are needed, and until the present moment, no studies were found that compared traditional acupuncture with LA in individuals with chronic nonspecific neck pain. There is a need for thorough research concerning LA, with robust methodologies, large sample sizes, and standardized and reproducible parameters, in order to increase understanding of this therapy and establish possible future clinical applications [30, 49, 50].

### Objectives {7}

The aim of this study is to compare the effects of traditional acupuncture and laser acupuncture therapies in individuals with chronic nonspecific neck pain.

#### The primary objective

The primary objective is to assess the pain intensity at rest and during cervical active movements (flexion, extension, left and right lateral bending, and left and right rotation) using the Numerical Rating Scale (NRS), immediately after the end of the therapies and with follow-up after 1 month.

#### The secondary objective

The secondary objective is to evaluate the pain using pressure pain threshold (PPT); temporal summation (TS) of pain; conditioned pain modulation (CPM); global perceived effect (GPE), immediately after the end of the therapies; and consumption of analgesic medications for neck pain, and global perceived effect (GPE) will follow up after 1 month.

### Trial design {8}

This study will be a randomized controlled clinical trial (RCT) with a blinded assessor, conducted according to the established standards for reporting clinical trials: Consolidated Standards of Reporting Trials (CONSORT) and Standards for Reporting Interventions in Clinical Trials of Acupuncture (STRICTA). The acupuncture style adopted will be traditional acupuncture and laser acupuncture, and the protocol was developed following the recommendations of Standard Protocol Items: Recommendations for Interventional Trials (SPIRIT).

## Methods: participants, interventions, and outcomes

### Study setting {9}

The study will be undertaken at the Physiotherapy Department of the Federal University of São Carlos (UFSCar), in the city of São Carlos, São Paulo State, Brazil.

### Eligibility criteria {10}

After screening using an online form, the potential participants will be registered, and checks will be performed considering the inclusion and exclusion criteria.

### Inclusion criteria

Individuals will be recruited if they meet the following conditions: age between 18 and 60 years, complete primary education of both sexes, neck pain complaints (pain and stiffness, for a minimum period of 3 months, reported during screening), score ≥ 3 for pain intensity on the Numerical Rating Scale (NRS), consent to random allocation and present consent and in accordance with the conditions of the treatments, and possible adverse effects, presented and explained in the consent form.

### Exclusion criteria

Individuals will be excluded if they present fracture or history of vertebral injury, spondylolisthesis, spinal canal stenosis, ankylosing spondylitis, signs of radiculopathy, cancer, acute infections, hemorrhagic diseases, rheumatologic diseases, systemic inflammatory diseases, diagnostic changes in skin sensitivity, hearing deficits (uncorrected), difficulty in answering questionnaires, in conditions of pregnancy, puerperium and breastfeeding; individuals who have started or underwent any type of intervention or treatment in the last 3 months; individuals who will be orientated not to ingest any sedative, anti-inflammatory and analgesic medications (narcotics and non-narcotics), and any type of alcoholic substance in the last 48 h before the evaluation; individuals who do not comply with the conditions and treatments, or who refuse to participate in the research, will be excluded; individuals who could not remain in the ventral decubitus position, upper limbs along the body and cervical in neutral position during the time of interventions; and individuals will be free to discontinue the treatment at any time, and if they make the most recent data, they will be computed for analysis, as well as the reason for the interruption.

### Who will take informed consent? {26a}

Data collection will only start after the participants have signed an informed consent form, which will be explained by the evaluator.

### Additional consent provisions for collection and use of participant data and biological specimens {26b}

Not applicable for this study.

### Interventions

#### Explanation for the choice of comparators {6b}

No studies were found in the literature that effectively compared traditional acupuncture (TA) with laser acupuncture (LA) for the treatment of chronic nonspecific neck pain. Therefore, the proposed research will focus on evaluating and comparing the changes in pain symptoms and neck functional capacity, after the application of TA and LA in cases of chronic nonspecific neck pain.

#### Intervention description {11a}

The interventions will follow a standardized therapy protocol, and the assessments will be performed immediately before and after the single treatment session. Four acupuncture points (*Tianzhu*, *Fengchi*, *Jianjing*, and *Jianzhongshu*) will be stimulated bilaterally with needles, laser, or sham. The participant will be positioned in a ventral decubitus position, upper limbs along the body, and cervical in neutral position and asked to rest for 5 min, prior to the intervention. At the locations where the therapies will be applied, the skin will be hygienized with gauze and 70% alcohol solution. A dermatograph pencil (COLOURED®) will be used to draw circles with diameters of 2 cm around the application points. The same researcher, an acupuncturist with specialization in the field and 9 years of clinical experience, will perform all the interventions (R3). The individuals will be asked not to use any other treatment for neck pain during the study period. All the data collected about the participants will be confidential (Fig. 1).

**Fig. 1 Fig1:**
[figure not shown]
Acupuncture points that will be used in therapies

##### Traditional acupuncture (TA)

For the TA group, the interventions will be performed using disposable Goldlife® needles (0.25 mm diameter, 40 mm length; Brazilian product registration number MS80553910002) supplied in packages containing 10 surgical steel needles and a needle guide tube. Using the guide tube, the needles will be appropriately positioned in the centers of the areas demarcated on the skin and manually inserted into the muscle to a depth of 20 mm. The acupuncture points (*Tianzhu*, *Fengchi*, *Jianjing*, and *Jianzhongshu*) will be stimulated bilaterally. The manual needle stimulation technique known as sparrow pecking will be used [35, 51, 52]. After the stimuli, the needles will be left in position for 20 min [43, 46, 53], followed by the removal using a stainless steel collecting cup and disposal in an appropriate container for sharps (Descarpack®), in each session, new needles will be used.

##### Laser acupuncture (LA)

For the LA group, the interventions will be performed using Recover® laser (MMO, São Carlos, SP, Brazil). The laser will be placed at the specific acupuncture points: Tianzhu, Fengchi, Jianjing, and Jianzhongshu. The laser tip (0.03 cm^2^ of beam area) will be positioned with the “probe” head directly on the acupuncture point, in a perpendicular position and in direct contact with the skin, and every point will be treated for 2 min, totaling 16 min of treatment, plus 4 min of rest, to standardize with the traditional acupuncture time, which is 20 min. The parameters (Table 1) are based on a previous work using LA for neck pain [46], following the criteria suggested by Baxter [50].

**Table 1 Tab1:** Laser acupuncture parameters

Parameters	Infrared laser
*Center wavelength [nm]*	*808*
*Operating mode*	*Continuous wave*
*Output power [mW]*	*100*
*Power density [W/cm*^*2*^*]*	*3.33*
*Beam profile*	*unique*
*Irradiance at target [W/cm*^*2*^*]*	*3.33*
*Energy density [J/cm*^*2*^*]*	*333*
*Total time per point [s]*	*120*
*Radiant energy per point [J]*	*10*
*Number of points irradiated*	*8*
*Area irradiated [cm*^*2*^*]*	*0.03*
*Total radiant energy [J]*	*80*
*Angle of application*	*90°*
*Application technique*	*Contact*

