##### Sham [S]

For the sham group intervention [S], individuals should be treated with the same care as the current intervention group, including therapy time, attention to the individual, and temperature in the treatment room. The placebo intervention will be performed as a control for groups TA and AL. For the placebo intervention, the same device as the real intervention group will be used (Recover® from MMO, São Carlos, SP, Brazil); however, the treatment will be simulated with a laser probe disabled by the manufacturer, and the device maintain the common acoustic signals during therapy [16]. Participants will not be informed of the laser probe inactivation. The criteria for selecting points, parameters, and dose are identical to those used in the AL group (Table 1), including the time of application and placement of the probe at the acupuncture points: Tianzhu, Fengchi, Jianjing, and Jianzhongshu.

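### Table 1 gives two incompatible laser doses: the stated power and time deliver 12 J per point (96 J in total), but the table states 10 J (80 J)

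*Protocol article*

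**What the plan says.** In the Laser acupuncture (LA) section, the text sets the exposure by time: "every point will be treated for 2 min, totaling 16 min of treatment, plus 4 min of rest". The rest is there to bring the session to the 20 min of the needle arm.

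Table 1 in the same section lists:

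- operating mode: "Continuous wave"
- output power: 100 mW
- beam area: 0.03 cm² (also given in the text)
- power density: 3.33 W/cm²
- time per point: 120 s
- number of points: 8
- energy per point: 10 J
- energy density: 333 J/cm²
- total energy: 80 J

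The Sham section refers back to the same table: "The criteria for selecting points, parameters, and dose are identical to those used in the AL group (Table 1". It also copies the application time.

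**The concern.** For a continuous-wave laser, the energy at a point is power multiplied by time. Energy density and total energy then follow from the beam area and the number of points. Table 1 gives both the inputs and the results, and they disagree.

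Dose is the content of the experimental arm, and treatment is a single session, so a wrong setting cannot be corrected at a later visit. As written, a reader cannot tell whether the trial tests 80 J or 96 J, and the published dose may not be the dose given. The protocol's own Background asks for standardized, reproducible laser parameters in this field. The 16 + 4 min timetable, and with it the match to needle time, rests on the same figures.

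**Working it through.** **Inputs**, all from the Laser acupuncture (LA) section and its Table 1: power P = 100 mW = 0.1 W, continuous wave; beam area A = 0.03 cm²; time per point t = 120 s; number of points n = 8.

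**What reproduces**

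- Power density: P/A = 0.1/0.03 = 3.33 W/cm², as stated. Power and area agree with each other.
- Irradiation time: n × t = 8 × 120 s = 960 s = 16 min, and 16 + 4 = 20 min, as stated.
- The three energy figures agree among themselves: 10/0.03 = 333 J/cm² and 10 × 8 = 80 J.

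**What does not reproduce**

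| Quantity | Formula | From stated power and time | Table 1 | Ratio |
|---|---|---|---|---|
| Energy per point | P × t = 0.1 × 120 | 12 J | 10 J | 1.20 |
| Energy density | 12/0.03 | 400 J/cm² | 333 J/cm² | 1.20 |
| Total energy | 12 × 8 | 96 J | 80 J | 1.20 |

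**Which time the energy figures imply**

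- From energy per point: 10 J / 0.1 W = 100 s.
- From energy density: 333/3.33 = 100 s.
- From total energy: 80 J / 8 = 10 J per point, so again 100 s.

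At 100 s per point, irradiation lasts 8 × 100 = 800 s = 13.3 min. With the 4-min rest the session is 17.3 min. Reaching 20 min would need a rest of 20 − 13.3 = 6.7 min.

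**Other explanations tried**

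- *Rounding.* It cannot produce a 20% gap.
- *Duty cycle.* None applies in continuous-wave mode.
- *Lower true power.* 10 J in 120 s needs 10/120 = 83.3 mW, hence 0.0833/0.03 = 2.78 W/cm². Table 1 says 100 mW and 3.33 W/cm².
- *Different beam area.* 12 J at 333 J/cm² needs 12/333 = 0.036 cm². The power density would then be about 2.78 W/cm², not 3.33, and the energy per point would still be 12 J, not 10.
- *One mistyped cell.* The 120 s is repeated in the text as 2 min and again in the 16-min total, while three energy cells agree with one another. No change to a single cell reconciles the section.
- *Repositioning counted in the 120 s.* The text counts all 16 min as treatment and lists the rest separately.

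**The case against.** The strongest reply is that the working instruction is given by time and is consistent: 2 min per point, 16 min in all, 20 min with rest, and 120 s in the table. Power, mode, area and number of points fit it. On that reading only the three derived cells are wrong, and the operator is never told to dose by energy. This is the likelier reading, but the document does not prove it, because the device may be programmed in joules.

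The practical harm is also limited:

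- One acupuncturist gives every treatment from a script, so dose drifting between participants is not the main worry. The realistic risk is a misreported dose.
- The sham probe emits nothing and copies the laser arm's application time. Sham and laser stay matched whichever time is true, and blinding between them is not affected.
- The 20-min match fails only if the energies govern and the rest stays at 4 min. Since the rest exists to reach 20 min, it could be lengthened.
- Nothing in the protocol shows that 12 J rather than 10 J per point changes efficacy or safety.

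All of this stands as a limit on the consequences. It does not remove the contradiction, and it does not tell a reader which dose was tested.

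**Conclusion.** The concern holds. Table 1 contains one prescription by time (120 s, which gives 12 J, 400 J/cm² and 96 J) and another by energy (10 J, 333 J/cm² and 80 J, which gives 100 s). They differ by 20%. The result rests only on the stated power, mode, area, time and number of points, and needs no outside source.

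Which side is wrong cannot be decided from the protocol. Randomization, the outcomes, sample size, alpha and power are not touched. It is still more than a clerical slip, because the dose defines the active arm and any replication or pooled analysis would rely on it. It must be corrected.

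**What to change.** Check the setting programmed on the device, then correct whichever side is wrong:

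- **If 120 s at 100 mW is used:** change Table 1 to 12 J per point, 400 J/cm² and 96 J in total. The 16 + 4 min text stands.
- **If 10 J per point is programmed:** change the time to 100 s per point in table and text, irradiation to 13.3 min, and the rest to about 6.7 min so that the session still lasts 20 min.
- **If the true power is not 100 mW:** correct power, power density and the energy cells together.

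Apply the same timing to the sham. If participants have already been treated, report the setting actually used. Notify the ethics committee, and the registry where its record carries these figures.

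The cost is one check of the device and an edit to the table and text. No extra participants or assessments are needed.

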##### Sham [S]

For the sham group intervention [S], individuals should be treated with the same care as the current intervention group, including therapy time, attention to the individual, and temperature in the treatment room. The placebo intervention will be performed as a control for groups TA and AL. For the placebo intervention, the same device as the real intervention group will be used (Recover® from MMO, São Carlos, SP, Brazil); however, the treatment will be simulated with a laser probe disabled by the manufacturer, and the device maintain the common acoustic signals during therapy [16]. Participants will not be informed of the laser probe inactivation. The criteria for selecting points, parameters, and dose are identical to those used in the AL group (Table 1), including the time of application and placement of the probe at the acupuncture points: Tianzhu, Fengchi, Jianjing, and Jianzhongshu.

#### Criteria for discontinuing or modifying allocated interventions {11b}

There will be no changes in the allocations and no migration of individuals between the groups will be allowed. If individuals discontinue treatment, recent data will be computed for the analyses according to the intention-to-treat principle, and the motive for the desistence will be recorded.

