#### Strategies to improve adherence to interventions {11c}

To minimize data loss, all the participants in the trial will receive a card with the date and time of session. The therapist responsible for the session will send a WhatsApp message from a cellphone account used only for this research, confirming the session, 1 day in advance. For the evaluations and reevaluations, the blinded evaluator will contact the participants by WhatsApp, confirming the initial and final evaluations, as well as the follow-up 1 month after the end of the intervention, which will be performed by telephone. In cases of abandonment or impossibility of continuing the study, the data will be analyzed according to an intention-to-treat protocol.

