### Sample size {14}

The calculation of the sample size considered a difference of 1.5 points between the groups, which would be a clinically relevant value for the outcome of neck pain intensity, as measured using the Numeric Rating Scale (NRS) [64, 66], with an estimated standard deviation of 1.6 points, based on a scientific clinical study [43]. There are a statistical power of 80% and a possible sample loss of 20%, considering individuals who for any reason want to interrupt the intervention. Thus, 84 individuals will be needed in total, 28 in each group (TA, LA, and Sham). The processing of the sample calculation was performed using the Minitab software, v.17, State College, PA.

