#### Plans to promote participant retention and complete follow-up {18b}

The participants will be provided with guidance when they sign the informed consent form and commit to attending on the scheduled treatment dates. They will receive a card with the dates of the treatment sessions, a contact telephone number, and a WhatsApp contact number used only for this research. This will ensure that they receive the necessary attention and will assist in fully accompanying them during the research. If individuals abandon the trial, the reasons will be recorded, the most recent data will be computed, and analysis will be performed using the intention-to-treat principle.

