### Methods in analysis to handle protocol non-adherence and any statistical methods to handle missing data {20c}

In the case of discontinuity, missing data will be handled by adopting the intention-to-treat principle, in order to make statistical inferences.

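### The plan does not separate stopping the single session from leaving the study, so its recent-data rule could replace outcomes that are still obtainable with the pre-session score

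*Protocol article*

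**What the plan says.** All references are to the protocol article.

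- On stopping treatment, Criteria for discontinuing or modifying allocated interventions {11b} says: "If individuals discontinue treatment, recent data will be computed for the analyses according to the intention-to-treat principle". Exclusion criteria carries the same rule: "individuals will be free to discontinue the treatment at any time, and if they make the most recent data, they will be computed for analysis".
- On leaving the study, Plans to promote participant retention and complete follow-up {18b} says: "If individuals abandon the trial, the reasons will be recorded, the most recent data will be computed".
- On missing data, section {20c} says: "In the case of discontinuity, missing data will be handled by adopting the intention-to-treat principle".
- On planned loss, Sample size {14} allows for "a possible sample loss of 20%, considering individuals who for any reason want to interrupt the intervention".
- On timing, Intervention description {11a} says that "the assessments will be performed immediately before and after the single treatment session". The laser section gives the session length when it adds rest time "to standardize with the traditional acupuncture time, which is 20 min". The primary objective needs the NRS immediately after therapy and at 1 month. Strategies to improve adherence {11c} lists the evaluations to be confirmed with participants, "as well as the follow-up 1 month after the end of the intervention, which will be performed by telephone".

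**The concern.** Stopping a treatment and leaving a study are different events. An intention-to-treat analysis needs the outcomes of people who stop treatment, observed and counted in the arm to which they were allocated. Here one instruction covers both events, and it points to data already held. For someone who ends the session partway, the only NRS then held is the pre-session one.

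Those later outcomes need not be missing. The participant is still on site for the post-session NRS, and the 1-month NRS needs only a telephone call. If they are not collected, no later analysis plan can recover them.

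Interruption may also differ between arms. By the article's own description, traditional acupuncture (TA) inserts needles 20 mm into muscle with manual stimulation, laser acupuncture (LA) is painless, and Sham uses a disabled probe. If more people stop in TA, replacing their outcomes with baseline would affect the TA–LA and TA–Sham comparisons more than LA–Sham.

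**Working it through.** **1. The passages side by side.**

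| Event | Section | Instruction |
|---|---|---|
| Stops treatment | {11b}, Exclusion criteria | use (most) recent data |
| Abandons the trial | {18b} | use most recent data |
| Discontinuity, undefined | {20c} | treat as missing data, under intention-to-treat |
| Interrupts the intervention | Sample size {14} | counted in the 20% loss |

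None of these sections says that a person who stops the session continues to the remaining assessments, and none gives different handling for the two events.

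**2. What the rule yields for someone who stops partway.** The NRS is scheduled before the session, immediately after it, and at 1 month. At the moment of stopping, only the first exists. Using it at both later time points records a change of zero at each.

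**3. The plan's sample size.** Inputs from Sample size {14} are a difference of 1.5, SD 1.6, power 80% and 20% loss. Alpha 0.05 comes from Statistical methods {20a}. I assumed a three-group one-way ANOVA with noncentrality n × (1.5²/2)/1.6².

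- 22 per group gives 78.1% power and 23 per group gives 80.1%, so 23 are needed.
- 23 × 1.2 = 27.6, rounded up to 28; 3 × 28 = 84.

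The stated 84 reproduces. It does not depend on the present point.

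**4. Possible size of the distortion.** Let p be the share of an arm that stops early and is held at baseline, and d the mean change those people would have shown.

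- Error in the arm mean = p × d.
- Error in a TA contrast = p(TA) × d(TA) − p(other) × d(other).

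The documents give neither p nor d. The values below are assumptions for TA. The contrast is off by the full amount only if nobody stops in the other arm.

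| p | d (points) | Error in TA mean | Share of 1.5 |
|---|---|---|---|
| 5% | 1 | 0.05 | 3% |
| 5% | 2 | 0.10 | 7% |
| 20% | 1 | 0.20 | 13% |
| 20% | 2 | 0.40 | 27% |

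With 28 per arm, 5% is 1.4 people and 20% is 5.6.

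**The case against.** The best reply is that no section tells the site to stop following anyone. The sentence in {11b} is about analysis, and recent data could include a post-session score taken minutes after an early stop. Section {11c} has the evaluator contact participants for the final evaluation and the 1-month call, and Provisions for post-trial care {30} says individuals will be monitored for a month and reassessed by phone. Neither makes an exception for people who stop early. The article is also condensed, so operational detail may sit in the full protocol.

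Much of this stands. The point cannot be put as a rule that ends follow-up. What remains is the wording that is stated: one fall-back for two different events, and an allowance for loss tied to interruption.

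Three stronger readings are tempting but unsupported:

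- A reader might infer that 20% of 84, about 17 people, would lack obtainable outcomes. The 20% is a planning allowance for any reason, not a forecast of people stopping a short session, and some of those people may refuse all further contact.
- A reader might infer that confidence intervals widen by about 13%, from 1.6 × √(2/28) = 0.43 to 1.6 × √(2/22) = 0.48. That assumes interrupters leave the analysis. The article says their data are used, so 28 per arm remain.
- A reader might infer that interrupters are excluded, because Exclusion criteria lists non-compliance and inability to hold the prone position during the intervention. The same section says that data from people who discontinue are analysed.

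**Conclusion.** The point holds as a fault in stated wording. The article does not distinguish stopping the session from leaving the study. Applied literally, its fall-back would replace post-session and 1-month values that can still be obtained with the pre-session NRS. That records no change for those people, and could bias the TA contrasts if needling is interrupted more often than laser or sham.

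The size is unknown and may be small. The range of 0.05 to 0.4 points rests wholly on assumed interruption rates and changes, and on no interruption in the comparison arm. The upper end needs one TA participant in five to stop a single session and still change by 2 points. Early stopping that is rare, or similar across arms with similar changes, would leave little distortion of the contrasts. The planned sample size needs no change. The correction is worth making because it is cheap and must be in place before data are collected.

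**What to change.** - In {11b} and Exclusion criteria, state that stopping or shortening the session is not withdrawal. The post-session assessment and the 1-month call go ahead for every randomised participant unless that person withdraws from follow-up, and the observed values are analysed in the allocated group.
- In {11b}, {18b} and {20c}, limit the recent-data rule to outcomes that truly cannot be obtained.
- Record two things separately: whether the session was stopped (how much was completed, and why) and whether the participant left the study.
- In Sample size {14}, describe the 20% as participants without an outcome assessment.

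The cost is wording and two fields on a form. The assessments and calls are already scheduled and staffed. The drawback is that a participant who stopped early is asked to stay for a short assessment and may refuse. The change concerns data collection only and leaves the right to stop as it is.
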